### Practitioner and patient retention

Retention will be facilitated through the practitioner and patient remuneration for each of the separate study procedures. *Patients* will be eligible for remuneration once they complete the mHealth questionnaire on day 23. The total remuneration amount will depend on the number of mHealth questionnaires completed. *Practitioners* will be eligible for remuneration at the end of the observational study phase after completing the UTAUT questionnaire. In addition, those who participate in the debriefing/interview session will receive additional remuneration.

### Training of providers and staff

Training for the participating Network staff and providers is executed using a “train the trainer” model. The study team will train Network Coordinators who in turn train the participating practitioners. Training of the Coordinators is done online using slides, a training guide, and a short guide. A series of training videos about using FollowApp.Care and the EDC are also made available to Coordinators and Practitioners. Training included the following: (1) general information about the study (i.e., contact information, study overview, structure, and use of the platform) and (2) specific information (i.e., recruitment, informed consent, data collection, and use of the Network EDC for data entry). Competency is assessed by the use of the FollowApp.Care platform and entering data in the database using mock participants. See Table 4 for an overview of the development process and the training tools.

**Table 4 Tab4:** Overview of the training development process and training tools

Training Development Process	Training Tools
Draft by research team	Slides and videos
Cascading review by Coordinators	Quick Guide
Review by NDPBRN Executive Committee	Training Manual
Review by NIH Program Officer	Screening & Enrollment log
Approval by NIH	Screening workflow

### Sample size

A minimum of 150 and up to 215 dental providers will be recruited, and each provider will be expected to enroll an average of 21 patients for a total of 3147. Assuming a 40% missing data rate among enrolled patients throughout the duration of the study, there will be 1888 patients remaining. This includes patient non-response rates as well as item non-response rates for the outcome of interest during the study period. Given a sample of 1888, the GLMM model for repeated measures will be able to detect a 20% reduction in pain intensity between procedure groups over time with 80.0% power. The minimum sample size was derived by the “longpower” sample package in the R statistical computing environment.

### Statistical analysis

Standard descriptive statistics will be used to describe both patient and practitioners’ characteristics using 5 data capture methods: 1) the SUS questionnaire, 2) the mHealth Questionnaire distributed on pre-specified days post procedure, 3) the UTAUT questionnaire, 4) the debriefing/interviews, 5) and the practitioner eCRF. Summary statistics such as means, medians, and ranges will be produced for all measured continuous variables. Frequencies and percent contributions will be computed for all categorical and ordinal variables. Graphical methods like X-charts will examine distributions over time and identify potential, influential time points. The balance of baseline characteristics and measures between groups will be compared using appropriate tests, including chi-squared tests, student t-tests, and Wilcoxon rank-sum tests.

A challenge for this non-randomized study is confounders – pre-existing variables that affect the outcomes and differ between the treatment groups. In order to reduce bias, potential confounders variables will be adjusted in regression models for the analysis. Once participants discontinue the study, they will not be contacted and will not be replaced as the power calculation has accounted for them. If the discontinuation rate is high, the study team PIs will discuss how to proceed with the Network and NIDCR. We will create a missing category for all missing data and assess the need for any imputation methods.

We will estimate the difference in intensity, pain interference, and patient satisfaction dependent on the treatment type. The relative risk (RR) will be the measure of association reported along with 95% confidence intervals. Pain, interference, and satisfaction at the end of the study will be compared among the treatment categories. To model the differential treatment (CDT Grouping) effect on patients’ pain intensity, interference, and satisfaction, on, we will use GLMMs using a Poisson link. Models will include time, treatment type, age, gender, race/ethnicity, medications, and no medication methods as fixed effects. In addition, dentist and Network regions will be included as random effects in the models to account for correlations within clusters.

A secondary analysis will be considered for additional evaluation of the FollowApp.Care platform by the practitioners including assessment of usability and evaluation of fidelity. Means and corresponding estimates of precision (e.g., standard deviations and 95% confidence intervals) and frequency distributions with percentage contributions will be used to report the distribution of each metric. In addition, we will conduct a confirmatory factor analysis (CFA) for multilevel data to test the reliability and construct validity.

All statistical analyses will be performed at the standard significance level (α = 0.05) using R and Stata Statistical Software release 15 for StataCorp LP.

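### The missing-category rule for all missing data leaves confounders partly unadjusted in a non-randomised comparison and has no meaning for the outcome scores

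*Protocol article*

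**What the plan says.** Under Statistical analysis, the protocol article describes confounding as a challenge of the non-randomised design and answers it with covariate adjustment in the regression models. It then gives one rule for missing values: "We will create a missing category for all missing data and assess the need for any imputation methods". The Limitation section repeats the sentence, again straight after the remark on confounding. Neither place separates covariates from outcomes.

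For pain intensity, interference and satisfaction, "we will use GLMMs using a Poisson link". The fixed effects listed are time, treatment type, age, gender, race/ethnicity, medications and non-medication methods. Dentist and Network region are random effects.

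The Sample size section states: "Assuming a 40% missing data rate among enrolled patients throughout the duration of the study, there will be 1888 patients remaining". It defines that rate: "This includes patient non-response rates as well as item non-response rates for the outcome of interest during the study period".

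**The concern.** The rule raises two separate problems.

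**Covariates.** A missing category for a confounder is the missing-indicator method. Among patients in that category, procedure groups are compared without regard to the true confounder value. The fitted procedure effect is therefore a blend of an adjusted contrast (value known) and a crude one (value unknown). This happens even if values are lost purely by chance. The usual defence of the method is that randomisation balances the covariate between groups, and that is not available here. Some covariates could well be missing: patients are only encouraged to complete the pre-procedure questionnaire, and medication use is self-reported on the follow-up questionnaires.

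**Outcomes.** The three outcomes are 10-point scores in a Poisson model. A category labelled missing has no numeric value there, yet the rule covers all missing data, and the only missingness that the document quantifies is in the outcomes.

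At stake is the comparison between procedure groups in Hypotheses 1 to 3, where adjustment is the only protection against confounding.

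**Working it through.** **1. The plan's own figure.** 3147 enrolled and 40% missing, both from Sample size: 3147 × (1 − 0.40) = 1888.2, which reproduces the stated 1888. The plan thus counts 3147 − 1888 = 1259 patients as lost. A rule that keeps patients in a missing category does not fit that count.

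**2. Assumptions for the covariate check.** The document gives no confounder strength, group imbalance or covariate missingness, so all of these are assumed: a binary confounder with 50% prevalence; two procedure groups; a share p of patients with the confounder in group 1, and 1 − p of those without it; confounder rate ratio R; Poisson outcome; true group ratio 1.00; confounder missing completely at random in a fraction m.

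**3. Bias with no adjustment.** Crude ratio = [pR + (1 − p)] / [(1 − p)R + p].
- Mild (R = 1.3, p = 0.6): 1.18 / 1.12 = 1.05
- Middle (R = 2, p = 0.7): 1.7 / 1.3 = 1.31
- Strong (R = 3, p = 0.8): 2.6 / 1.4 = 1.86

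**4. Bias with a missing category.** The model has three covariate levels: absent, present and missing. The fitted ratio θ makes observed and fitted events in group 1 agree when summed over the three levels. In the middle case with m = 0.4, taking the event rate without the confounder as 1:

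0.6 × [0.15 − 0.5 × 0.15θ/(0.15θ + 0.35) + 0.70 − 1.0 × 0.35θ/(0.35θ + 0.15)] + 0.4 × [0.85 − 1.5 × θ/(θ + 1)] = 0

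At θ = 1.126 the first part is −0.022 and the second +0.022, so θ = 1.126. The share of log-scale bias remaining is ln 1.126 / ln 1.308 = 0.44.

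**5. Simulation of the middle case (n = 400,000).** Crude ratio 1.31; fully adjusted 1.00.

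| Covariate missing | Missing category | Complete cases, adjusted |
|---|---|---|
| 10% | 1.03 | 1.00 |
| 20% | 1.07 | 1.00 |
| 40% | 1.13 | 1.00 |

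The rule does worse here than dropping the affected patients, although dropping them loses precision.

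**6. Range over R = 1.3 to 3 and p = 0.6 to 0.8.**

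| Covariate missing | Log-scale bias remaining (simulation) | Spurious ratio (truth 1.00) |
|---|---|---|
| 10% | 8–16% | 1.01–1.09 |
| 20% | 20–29% | 1.01–1.19 |
| 40% | 41–52% | 1.02–1.37 |

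Solving the step 4 equation over the same range, without simulation noise, gives 10–15%, 21–28% and 41–51%, inside the simulated ranges.

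**7. Outcomes.** No arithmetic applies. A Poisson model needs a count for each record. A record without a score contributes nothing to the likelihood, and a category label cannot supply a score.

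**The case against.** **The 40% is not a covariate rate.** A reader might join "Assuming a 40% missing data rate among enrolled patients throughout the duration of the study" to the missing-category rule and conclude that about half of the confounding will survive. The document does not support that: its definition ties the 40% to patients and to items of the outcome. Covariate missingness may be lower, since demographics are collected before the procedure and also appear on the practitioner's case report form, and procedure type comes from that form. This objection stands, so the figures above are a range under assumptions and not a forecast.

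**Baseline pain is not a safe example.** It is an obvious candidate confounder, but it appears only among other covariates under Study outcome measures and not in the listed fixed effects. If it is left out of the model, its confounding remains whatever the missing-data rule. The mechanism shown applies to any confounder that is adjusted for.

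**The bias need not rival the planned effect.** The study is sized to "detect a 20% reduction in pain intensity between procedure groups over time with 80.0% power". A 20% reduction is a ratio of 0.80, or 1.25 inverted. A spurious ratio above that arises only in the strongest corner of the range at 40% covariate missingness. In mild cases the bias is trivial.

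**The outcome wording may be only loose.** One might infer that missing pain scores will be coded as a category and corrupt the primary analysis. Nothing says so: Sample size treats those patients as lost, and a repeated-measures mixed model would use the scores that exist. For outcomes, the fault is a rule that cannot be applied, not a demonstrated bias.

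**Imputation is left open.** The same sentence promises to assess the need for it, and the method and sensitivity analyses may properly be set out in an analysis plan that is not shown. Their absence is no finding. But the promise names nothing that would displace the stated default, and that default is wrong for this design.

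**Conclusion.** The point holds as a fault in a stated rule. For confounders, a missing category leaves part of the confounding in place even under missing completely at random. In the assumed scenarios the share left is close to the missing fraction or somewhat above it, and the resulting ratio depends heavily on confounder strength and group imbalance: from negligible to 1.09 at 10% missing, and from 1.02 to 1.37 at 40%. The actual size in this study cannot be stated, because no covariate missingness rate is given. For the outcomes, the rule cannot operate in the named model and disagrees with the sample size section's own accounting. The documents do not show that 40% of confounder values will be missing, that the bias will exceed the effect the study is sized for, or that non-response depends on pain.

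**What to change.** Delete the missing-category sentence under Statistical analysis and under Limitation. Replace it with two statements:

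- **Outcomes:** the models use every observed visit by likelihood, which is valid under missing at random given a suitable model, and no category is created for a missing score.
- **Adjustment covariates:** missing values are handled by multiple imputation, with procedure group, dentist and the observed pain scores in the imputation model.

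A delta-adjusted sensitivity analysis for outcome non-response would be useful, but it is optional and can be left to the statistical analysis plan.

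The cost is a wording change and modest programming, chiefly to respect the clustering by dentist in the imputation. No new data are needed.

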## Objectives

### Primary objective is

To assess post-operative pain experiences by dental procedure type through 21 days post-procedure as reported by patients following study-eligible dental procedures and assess patients’ satisfaction with pain management following dental surgical procedures.

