## Hypotheses

The study includes the following hypotheses:

### Hypothesis 1

There is a significant difference in pain intensity measured over time and the dental procedure groupings after adjusting for pain management strategies and other complications. More specifically, are their significant variations in pain intensity due to different treatments after adjusting for:pain management strategy (e.g., pain medications used, adherence to pain management strategy, the usage of non-medicine methods for pain)other complications

### Hypothesis 2

There is a significant difference in pain interference measured over time and the dental procedure groupings, after adjusting for pain management strategies and other complications. More specifically, are their significant variations in pain interference due to different treatments after adjusting for:pain management strategy (e.g., pain medications used, adherence to pain management strategy, the usage of non-medicine methods for pain)other complications

### Hypothesis 3

There is a significant difference in patient satisfaction measured at the end of the 7-day period and dental procedure groupings, after adjusting for pain management strategies and other complications. More specifically, are their significant variations in patient satisfaction due to different treatments after adjusting for:pain management strategy (e.g., pain medications used, adherence to pain management strategy, the usage of non-medicine methods for pain)other complications.

### Hypothesis 4

Reported technology acceptance metrics; performance expectancy (PE), effort expectancy (EE), social influence (SI), and behavioral intention (BI) will be consistent with high acceptance of the FollowApp.Care platform.

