## Design and methods

### Study design

POPS is a longitudinal, prospective cohort study that will be conducted with practitioners and their patients undergoing potentially painful dental procedures. Data about baseline pain intensity and patient demographics will be collected prior to the procedure. The patients will receive push notifications through text messages via the FollowApp.Care platform on their mobile devices which asks them to comprehensively record their pain experience at designated time intervals on days 1, 3, 5, 7, 14, and 21 following their procedure. At the end of the 1st week (day 7), they will be asked to report their satisfaction with their post-operative pain management. On Day 23, after the procedure, they will be requested to complete a questionnaire to measure the platform’s usefulness and ease of use. All participating practitioners will be invited to complete a questionnaire to assess the platform’s perceived usefulness and ease of use. A subgroup of practitioners will also be invited to participate in debriefing/interviews to qualitatively evaluate their experiences with using FollowApp.Care for managing their patients’ post-op pain.

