### Instruments for data collection

Specific instruments include:mHealth questionnaires

The mHealth Questionnaire #1 includes questions about pre-procedural pain and patient demographics. The mHealth Questionnaire #2 includes questions about pain intensity and pain interference. Pain intensity questions are based on the PROMIS Item Bank v.1.0 – Pain Intensity Scale [39]. On days 1, 3, 5, 7, 14, and 21, patients are asked: “What is your level of pain right now?” On day 7, patients are also asked: “How intense was your pain at its worst since the procedure?” *Pain Interference* questions were taken from the validated Oral Health Impact Profile-14 (OHOP-14) [40] and the Revised American Pain Society Patient Outcome Questionnaire (APS-POQ-R) [41–43] questionnaires to focus attention on the small subset of activities (e.g., sleep) common to post-operative dental patients. If, on days 14 and 21, patients answer the pain intensity question (“What is your level of pain right now?”) as positive (> 0), they will also be asked the six pain interference questions. The mHealth Questionnaire #2 will also collect the following additional information: type and frequency of pain-relief medications taken and the presence of concurrent symptoms such as bleeding, visible swelling, suppuration (pus), and/or fever. The mHealth Questionnaire #3 includes questions from the 2nd mHealth questionnaire and questions about patient pain management satisfaction (see Additional file 1: Appendix 1).2.System Usability Scale (SUS) questionnaire

*FollowApp.Care usability as perceived by patients will be measured* by the system usability scale (SUS) [44–46] questionnaire to measure the usefulness and ease of use of the FollowApp.Care platform. The validated SUS is a simple questionnaire that uses a ten-item attitude Likert scale, giving a global view of subjective usability assessments (see Additional file 2: Appendix 2).3.Unified Theory of Acceptance and Use of Technology (UTAUT)

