### Study activities and data collection

Participating patients will be encouraged to complete the mHealth Questionnaire #1 prior to the procedure. Baseline pain intensity and patient demographic variables will be collected through the welcome message. *Type of procedure* (CDT) will be collected through the eCRF. *Practitioner demographic* variables, *specialty, and years in practice* will be collected through the practitioner’s enrollment questionnaire (EQ). This information is already available in the practitioner database, and enrolled practitioners will be asked to update their EQ before the study. *Practitioner years in practice* will be collected through the practitioner’s enrollment questionnaire (EQ).

Upon completing their procedures, all enrolled patients will receive post-operative instructions and guidance according to the provider’s standard practice. Additionally, all enrolled patients will receive guidance about FollowApp.Care. At the end of each day, the research staff will retrieve the new patient profiles from FollowApp.Care and check the patient contact information for completeness. The patients will receive text/email notifications at pre-determined time intervals (e.g., 9 am) on Days 1,3,5,7,14, and 21 and will be prompted to complete the corresponding mHealth Questionnaire (Table 2). An additional comment/chat feature will enable patients to securely communicate more information to their dental care team through the FollowApp.Care system, when needed. All patients will receive usual clinical care and can contact their provider/clinic by phone/in person if they so desire. Practitioner assessment of *expected pain intensity* will be collected through the eCRF.

**Table 2 Tab2:** Overview of the instruments

Instrument	Completion Time	Content	Completed by
mHealth Questionnaire #1	Day 0 (pre-procedure)	- Pre-procedural pain - Patient demographics	Patients
mHealth Questionnaire #2	Days 1, 3, 5 and 14 and 21	- Pain intensity levels, medications used, bleeding, and swelling - Pain interference (if having pain on 14 and 21)	Patients
mHealth Questionnaire #3	Day 7	-Pain intensity levels, medications used, swelling -Pain interference -Satisfaction with pain management treatment	Patients
System Usability Scale (SUS) Questionnaire	Day 23	Patients’ perceptions of the usability of the FollowApp.Care user interface	Patients

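### The end-of-study comparison names a time when satisfaction is not asked and interference is asked only of patients still in pain

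*Protocol article*

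**What the plan says.** The Statistical analysis section of the protocol article states: "Pain, interference, and satisfaction at the end of the study will be compared among the treatment categories". It does not say which day ends the study. The same section plans one form of Poisson mixed model for intensity, interference and satisfaction, with time among the fixed effects.

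On timing, the primary objective is "To assess post-operative pain experiences by dental procedure type through 21 days post-procedure as reported by patients", and Study design has patients report "at designated time intervals on days 1, 3, 5, 7, 14, and 21 following their procedure". For satisfaction, Study design says "At the end of the 1st week (day 7), they will be asked to report their satisfaction with their post-operative pain management". Hypothesis 3 likewise refers to "patient satisfaction measured at the end of the 7-day period".

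For interference, Instruments for data collection says that patients whose current pain on day 14 or 21 is above 0 get a further set of items: "they will also be asked the six pain interference questions". Table 2 repeats the condition: "Pain interference (if having pain on 14 and 21)".

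On missing values, the Statistical analysis and Limitation sections say only that a separate category will be created for them and that the need for imputation will be assessed.

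**The concern.** Three outcomes with three different collection schedules are given a single comparison time. That time does not fit two of them.

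For satisfaction, the sentence points to a time at which nothing is scheduled and disagrees with the hypothesis that it serves.

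For interference, values on days 14 and 21 exist only for patients who still have pain. Pain intensity is measured after the procedure, and Hypothesis 1 expects it to differ between procedure groups. Comparing recorded interference late in follow-up therefore compares subsets that the procedure itself helped to select. A procedure from which most patients recover could look no better than one that leaves many in pain, because its recovered patients drop out of the comparison. The same gap affects the day-14 and day-21 records in the repeated-measures model for Hypothesis 2.

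Interference and satisfaction both belong to the primary outcomes, so the analysis time and the handling of patients not asked should be settled before data are seen.

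**Working it through.** **Schedule against analysis time** (Study design; Instruments for data collection; Table 2)

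| Outcome | Asked of all patients | Asked of some | Not scheduled |
|---|---|---|---|
| Intensity | days 1, 3, 5, 7, 14, 21 | – | – |
| Interference | days 1, 3, 5, 7 (implied by the contents of Questionnaires #2 and #3) | days 14, 21: only if current pain > 0 | – |
| Satisfaction | day 7 (Questionnaire #3) | – | days 1, 3, 5, 14, 21, 23 |

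The day-23 patient instrument is the System Usability Scale, which concerns the platform. The practitioner form at day 21 is not described as carrying a satisfaction item. Scheduled satisfaction values after day 7 are therefore 0. With one occasion per patient, and the same occasion for everyone, a time coefficient for satisfaction is not identifiable.

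**The plan's own sample figure.** 3147 × (1 − 0.40) = 1888.2, which reproduces the stated 1888. This is used below only to scale the counts.

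**How many would have day-21 interference values.** The article gives no day-21 pain prevalence, so a range is assumed.

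| Assumed share with pain > 0 | Patients with a value, of 1888 |
|---|---|
| 5% | 94 |
| 10% | 189 |
| 20% | 378 |
| 30% | 566 |

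**What the restriction does to a ratio.** Let p be the share in pain and m the mean interference among those in pain, for procedure groups A and B.

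- Ratio among those asked = m_A / m_B.
- Ratio in all patients, counting the pain-free as 0 = (p_A × m_A) / (p_B × m_B).
- The second is the first multiplied by p_A / p_B, so under zero scoring the distortion equals the prevalence ratio. It vanishes only if the groups have equal shares in pain.

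Assumed inputs:

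| p_A, m_A | p_B, m_B | Asked only | All patients |
|---|---|---|---|
| 0.20, 3 | 0.05, 3 | 3/3 = 1.0 | 0.60/0.15 = 4.0 |
| 0.20, 3 | 0.10, 3 | 3/3 = 1.0 | 0.60/0.30 = 2.0 |
| 0.20, 3 | 0.05, 4 | 3/4 = 0.75 | 0.60/0.20 = 3.0 |
| 0.30, 2.5 | 0.10, 4 | 2.5/4 = 0.625 | 0.75/0.40 = 1.875 |

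In the last two rows the two ratios point in opposite directions.

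**Limit of this calculation.** It concerns a single late day. Four of the six assessment days carry no pain condition, so the effect on a model across all days should be diluted. The article gives no means, variances or correlations from which to compute it.

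**The case against.** The end of the study is never defined, and the sentence can be read loosely as each outcome's last scheduled value. On that reading satisfaction is simply compared on day 7. This largely stands: a reader might infer that the satisfaction comparison has no data at all, but day-7 data exist and Hypothesis 3 already uses them. What remains is a conflict in the stated time and a time term that cannot be fitted.

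A reader might also infer that the plan puts recovered patients into its missing category. The article does not say so. Its Sample size section describes missingness as patient and item non-response, which a designed skip is not, and a missing category suits a categorical covariate better than a numeric score. This stands too. Even so, the blanket missing-data rule does not distinguish the two kinds of absent value, and nothing in the article scores the pain-free as zero.

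Finally, scoring gated items is ordinary material for an analysis plan, and that plan is not shown. If the omission were the whole point, this would settle it. But the article itself commits to an end-of-study comparison of an outcome that, by its own schedule, is recorded then only in patients with pain. A zero rule elsewhere would remove most of the difficulty, but the sentence as published would still need correcting.

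**Conclusion.** The point holds as a conflict between the analysis sentence and the collection schedule. For satisfaction, the stated time disagrees with Study design, Table 2 and Hypothesis 3, and the time effect is not estimable. For interference, a comparison of recorded values on day 14 or 21 is restricted by the intensity component of the same primary outcome, pain experience; it is not a selection on the interference score itself.

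The possible size is large for a single late day: 1.0 against 4.0 in the main illustration, and a reversal (0.625 against 1.875) in another. These figures rest on assumed prevalences and means, and the all-patient ratios also rest on scoring the pain-free as 0.

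It would be tempting to conclude that Hypothesis 2 as a whole gets a biased answer. The documents do not support going that far: interference is analysed over time, four of six days are ungated, and the effect on the full longitudinal estimate has not been quantified.

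**What to change.** Replace the sentence with an analysis time for each outcome.

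- **Intensity:** days 1 to 21.
- **Satisfaction:** day 7, in a model without a time term.
- **Interference:** keep follow-up through day 21, with a stated rule for days 14 and 21. Either score interference 0 when reported current pain is 0, or use a two-part analysis: the proportion in pain, then interference among those in pain. Add an analysis of days 1, 3, 5 and 7 as a sensitivity check.
- **Designed skips:** state that items not asked because current pain was 0 are not missing data, and keep them separate from non-response.

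The zero score should be labelled as an assumption. The screen asks about pain at that moment, with 9 am given as an example prompt time, while interference includes falling and staying asleep. A patient who is pain-free at the prompt may still have had a disturbed night.

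The cost is wording, with no new data collection. The small downside is that the late interference result rests on the stated zero assumption. Making days 1–7 the primary interference analysis would avoid that assumption but would narrow the 21-day primary objective, which is why it is better kept as a sensitivity check.
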